#### Complete blood counts and clinical chemistry

At each visit participants will have laboratory assessment of blood components to evaluate hepatic, renal, or hematopoietic toxicity performed at their local hospital laboratory. The tests performed include: a complete blood cell count panel with automated three or five part cell differential, electrolytes, glucose, creatinine, urea, alanine transaminase, aspartate transaminase, albumin, gamma glutamyl transferase and lipase. Adverse events from each participant will be assessed as laboratory results that exceed the local laboratory age-specific reference intervals. If participants are on a ketogenic diet during the study, then urine ketone testing will be performed to assess the consistency of the ketosis at each visit.

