## Methods/Design

### Objectives

#### The primary objectives of the CARE-E study are:

To determine if a CBD-enriched *Cannabis* herbal extract is safe and well-tolerated for pediatric patients with treatment resistant epileptic encephalopathy.To monitor the effects of a CBD-enriched *Cannabis* herbal extract on the frequency and duration of specific seizure types.

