##### *Study design*

The CARE-E trial is a phase 1, open-label, dose-escalation study consisting of 4 separate phases: recruitment, baseline, treatment, and weaning. The recruitment phase involves the selection of eligible participants using pre-established exclusion and inclusion criteria (described below). The baseline phase establishes baseline values for each experimental measurement prior to treatment with the study product. During the treatment phase, caregivers of participants administer dosages of the CBD-enriched *Cannabis* herbal extract twice daily to their children escalating at fixed one-month intervals over the course of four-months. Upon completion of the treatment phase, participants will enter the weaning phase and caregivers will slowly taper the participants off of the CBD-enriched *Cannabis* herbal extract using a one-month weaning schedule.

During the study, caregivers will monitor the participants for any potential side effects and will use a study diary to record their child’s seizure activity by tracking seizure frequency and duration, and any use of rescue medications to abort prolonged seizures. The participant’s condition as well as drug levels and biomarkers of toxicity will be monitored on a monthly basis. Testing will include blood and urine analysis, QoL assessments, neurological and general pediatric assessments, and an electroencephalogram (EEG) recorded for 2 h or until sleep is obtained (Fig. 1).

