Monthly follow-up: Caregivers will return to the clinic for the monthly testing as described above. Data from the study diaries will be copied for analysis. Following the completion of testing, parents will receive a new 33-day supply of the 1:20 THC:CBD *Cannabis* herbal extract from the research pharmacist. Parents will be instructed to administer the extract at increasing doses over the next 3 months; i.e. at 5–6 mg/kg/day divided BID at visit 3, 8–10 mg/kg/day divided BID at visit 4, and 10–12 mg/kg/day divided BID at visit 5. If the participant experiences significant side-effects at a certain dose, the subsequent CBD dose will be adjusted to the mid-point between their current dose and former dose. Parents will be instructed to continue tracking their child’s seizure activity and monitoring the child for potential side effects in the same manner as the initiation of therapy month.

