Weaning phase: Termination of treatment: At visit 6 (after completing 1 month of CBD at 10–12 mg/kg/day) participants will return to the clinic for a final series of tests which include: blood and urine analyses, quality of life and cognitive/developmental assessments, neurological and general pediatric assessments, and EEG. Participants will be provided with a one-month weaning schedule which incrementally decreases the dose of the 1:20 Δ^9^-THC:CBD *Cannabis* herbal extract administered (CBD at 8–9 mg/kg/day for 1 week then 5–6 mg/kg/day for 1 week then 2–3 mg/kg/day for 1 week prior to discontinuing the study product).

Final Assessment: Participants will return to the clinic upon completion of the one-month weaning period. Caregivers will provide observations of any side-effects noted during the weaning period and will complete a final quality of life questionnaire. Data from the seizure monitoring diaries will be collected and caregivers will be asked to return any leftover study drug.

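### Laboratory adverse events are defined as any result beyond the local reference interval, with no baseline or severity condition, so pre-existing and chance excursions enter the laboratory event count

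*Protocol article*

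**What the plan says.** The section on complete blood counts and clinical chemistry gives the rule: "Adverse events from each participant will be assessed as laboratory results that exceed the local laboratory age-specific reference intervals". The panel is "a complete blood cell count panel with automated three or five part cell differential, electrolytes, glucose, creatinine, urea, alanine transaminase, aspartate transaminase", followed by "albumin, gamma glutamyl transferase and lipase". The stated purpose is to detect liver, kidney and blood-forming toxicity.

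Testing is frequent: "At each visit participants will have laboratory assessment of blood components". The monthly follow-up text confirms this ("Caregivers will return to the clinic for the monthly testing as described above"), and at Visit 6 "participants will return to the clinic for a final series of tests which include: blood and urine analyses".

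Pre-treatment values exist. The study design section says "The baseline phase establishes baseline values for each experimental measurement prior to treatment with the study product", and the baseline phase lists blood analyses at the end of the run-in month. The laboratory rule does not refer to them.

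The first primary objective is to determine whether the extract "is safe and well-tolerated for pediatric patients with treatment resistant epileptic encephalopathy". A secondary objective relates dose escalation to the incidence of adverse effects. The trial is open-label with no control arm and aims for 28 children.

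**The concern.** The rule turns an abnormal value into an adverse event whether or not it arose on treatment and however small it is. Two kinds of value enter the count that say nothing about the extract.

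- **Pre-existing abnormality.** The exclusion criteria bar only clinically significant heart, kidney or liver disease, as judged by the site. Children stay on their existing anticonvulsants, and some may be on a ketogenic diet. A child can therefore enter with a mildly abnormal result and have it counted again at every dose level.
- **Chance.** A reference interval is normally set to leave out a small share of healthy values. With a long panel repeated monthly, many healthy children will have at least one result outside.

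With no control arm, the Visit 2 result is the only internal source for the background rate. The background section reports raised liver-enzyme activity in earlier CBD trials, which is a signal that this count should be able to separate from noise.

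The verb *exceed* is also loose. Read literally it covers high values only, whereas toxicity to the blood-forming system can appear as low counts.

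**Working it through.** The documents give no expected rate of out-of-range results, so there is no figure to reproduce.

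**Inputs**
- Analytes per visit, k: not stated. Assumed 18 = 4 (blood count) + 3 (differential) + 3 (electrolytes) + 8 (named chemistry tests). Range examined: 12 to 25.
- Chance q that one result is out of range with no drug effect: not stated. Assuming intervals that cover the central 95% of healthy children, q = 0.05 if either limit counts and 0.025 if only the upper limit counts.
- On-treatment visits with blood tests, v: 4 (Visits 3 to 6). The final assessment at Visit 7 lists no blood test.
- Children: 28.

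**Independent results.** P(at least one flag) = 1 − (1 − q)^(k·v).
- Either limit, one visit: 1 − 0.95^18 = 60.3%. Four visits: 1 − 0.95^72 = 97.5%. Expected flags: 72 × 0.05 = 3.6 per child, and 28 × 3.6 ≈ 101 in the trial.
- Upper limit only, one visit: 1 − 0.975^18 = 36.6%. Four visits: 1 − 0.975^72 = 83.8%. Expected flags: 28 × 72 × 0.025 ≈ 50 in the trial.

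**Correlated results.** Independence overstates the share of children flagged, because results in one child are related across tests and months. Normal results were simulated (20,000 children per setting) and flagged beyond ±1.96, or above +1.96 for the upper-limit reading. The table gives the share of children with at least one flag over four visits for 18 analytes. The last column leaves out any test that was already out of range at baseline.

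| Correlation between tests / between visits | Upper limit only | Either limit | Either limit, in range at baseline |
|---|---|---|---|
| 0.2 / 0.5 | 64% | 93% | 90% |
| 0.3 / 0.7 | 51% | 86% | 78% |
| 0.5 / 0.8 | 36% | 70% | 61% |
| 0.3 / 0.95 | 37% | 68% | 43% |

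In these four correlated settings, the either-limit share runs from 55% to 84% with 12 analytes and from 78% to 97% with 25. The upper-limit share runs from 29% to 53% with 12 and from 41% to 72% with 25.

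**What a baseline condition alone achieves.** It removes 19%, 33%, 44% and 71% of flagged results in the four rows. The share of children flagged falls much less unless results are very stable within a child. A baseline condition is therefore needed but is not enough; a severity or significance threshold must go with it.

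**The case against.** The strongest objections concern size and reach.

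- **The near-100% figure.** A reader might infer that almost every child will be flagged. That needs month-to-month independence within a child, which is implausible and contradicts the argument that pre-existing abnormalities persist. The correlated figures are the ones to use. On the high-only reading with strong correlation, fewer than half of the children are flagged, so a majority is not assured on every reading.
- **A false dose trend.** A reader might infer that the rule makes higher doses look worse. A chance rate that is constant across visits adds the same background at each dose step; it dilutes a trend and does not create one.
- **The primary outcome itself.** No section defines the primary endpoint as a count of laboratory flags. Caregiver reports and clinical assessments also inform safety, and the analysis is descriptive. The text on dose adjustment and escalation refers to significant side effects and dose-limiting toxicity, so the documents do not support reading these flags as driving dosing.
- **Missed low values.** An interval has two limits, and the section aims at blood toxicity, so outside either limit is the natural reading. The verb is ambiguous; it does not show that low values would be ignored.
- **Deferral to the SAP.** The statistical analysis section leaves full details to the SAP, where grading and shift tables commonly sit. Their absence here is not a fault.

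All five objections stand as limits. They do not remove the point, because the sentence is a definition that the article does state, and nothing else in it adds a baseline, grade or significance condition.

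**Conclusion.** The point holds as a fault in the stated definition. Followed as written, it counts chance and pre-existing out-of-range values as adverse events, in a trial with no control arm, although pre-treatment values are collected.

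Under 95% intervals, 18 analytes and four on-treatment visits, about 68-93% of children with no drug effect would have at least one flag when either limit counts and results are correlated. That is about 19 to 26 of 28. If only high values count, the range is about 36-64%, or about 10 to 18 of 28. Interval coverage, analyte count and correlations are all assumptions. The figures are for otherwise healthy children; more abnormal values at entry would raise the count, but the documents give no rate. The article also does not say whether laboratory events will be summarised per child or per result, so the size of the inflation is uncertain, though its direction is not.

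**What to change.** Replace the sentence with a definition along these lines: a laboratory adverse event is a result outside either limit of the local age-specific interval that is new or worse than the Visit 2 value, and that also rises by at least one grade on a prespecified toxicity scale or is judged clinically significant. The second condition must apply jointly with the first; offered as an alternative to it, every new trivial excursion would still count. For the same reason, the first step of the chosen scale should not simply be the reference limit. Using *fall outside* in place of *exceed* makes clear that low-side blood changes are included.

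Report all other out-of-range values in listings and in shift tables from Visit 2 by dose level. Give the proportion out of range at Visit 2, judged against the same limits, as the comparator for each dose step.

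The cost is one sentence, a named scale and a set of tables; the planned blood tests already supply the data. The downside is that minor excursions lose the label of adverse event, but they remain visible in the listings and shift tables. How far the threshold lowers the background cannot be calculated from the documents, which is why the Visit 2 proportion should be reported.

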#### Trough levels of anticonvulsants

Participants will remain on pre-existing anticonvulsant medications throughout the cannabis oil study period. Serum specimens will be collected from participants at each visit and trough levels of serum anticonvulsant medications will be determined by LC-MS/MS by the Roy Romano Provincial Laboratory Regina, SK, Canada. Serum specimens were collected and stored at − 20 °C prior to analysis. Adverse events will be counted if participants require a change in anticonvulsant medication during the trial either to maintain trough levels in the therapeutic range.

#### Quality of life assessment

The instrument we have chosen is the Quality of Life in Childhood Epilepsy (QOLCE-55) [14]. The QOLCE is a parent/proxy-completed measure of health-related quality of life specifically developed for children with epilepsy. It has several subsections containing multiple items, as well as a series of global ratings. The original tool was designed for individuals between 4 and 18 years of age which is one of the broadest age ranges for a tool of this kind. The tool allows for the rater to indicate that an item is not applicable if its content is above the age or developmental level of the child being rated. This makes the QOLCE potentially robust in the face of issues such as lower age and intellectual disability.

The QOLCE-55 shows good internal consistency and criterion-related validity as well as adequate to good test-retest reliability, depending on the subtest or item involved [14–16]. Areas covered include physical features (including physical limitations and fatigue), well-being (including depression, anxiety, helplessness and self-esteem), cognition (including attention, memory, language and general cognition), social engagement (including interactions, activities and stigma), and behavior. The QOLCE has also been shown to be sensitive to seizure activity and other clinical and psychosocial variables associated with epilepsy [14] and to benefits from treatments such as surgery [17]. Finally, the QOLCE has been used in the study of epileptic conditions with associated cognitive delays and Intellectual Disability and has already shown its utility in samples with Intellectual Disabilities [18]. While the QOLCE-55 was not exclusively positive in the wording of its items, most items were positively stated, making for less distress on the side of those completing the measure [19].

Ratings on the QOLCE are made on a 5-point scale with 1 titled “very often” and 5 titled “never.” Reversed items are recoded when scoring such that higher scores mean more positive outcomes. These scores are then recoded as follows: 1 = 0, 2 = 25, 3 = 50, 4 = 75, and 5 = 100. The mean for each of the subscales is then found by adding these values together and dividing by the number of items not marked Not Appropriate. The total score for the scale is the unweighted mean of the four subscales.

As well, for the purposes of our study we added 13 additional items based on reports from parents. Additional items covered sleep (including being drowsy), verbal and nonverbal communication, use of books, awareness of surroundings, interpersonal interactions with children and adults, and irritability. These additional items are scored as other QOLCE items and are summed into their own total score as well as being looked at individually.

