##### *Study population*

The study will recruit participants between the ages of 1–10 years with an epileptic encephalopathy resistant to standard medical treatment. The study will aim to enroll 28 children from four Canadian cities (anticipated seven participants per site).

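### The 13 added quality-of-life items are summed rather than averaged, so their total depends on how many items apply to the child

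*Protocol article*

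**What the plan says.** All scoring rules are in the protocol article, Experimental measurements, Quality of life assessment.

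- **Item values.** Ratings from 1 to 5 are rescaled to 0–100: "These scores are then recoded as follows: 1 = 0, 2 = 25, 3 = 50, 4 = 75, and 5 = 100".
- **Not-applicable option.** "The tool allows for the rater to indicate that an item is not applicable if its content is above the age or developmental level". The article relies on this option to extend the instrument to younger children and to children with intellectual disability.
- **Subscales.** The mean is found by "adding these values together and dividing by the number of items not marked Not Appropriate".
- **QOLCE-55 total.** "The total score for the scale is the unweighted mean of the four subscales".
- **Added items.** Thirteen items based on parents' reports cover, among other things, sleep, communication, books, contact with children and adults, and irritability. They are said to be scored in the same way as the other QOLCE items, and they "are summed into their own total score as well as being looked at individually". No divisor is given.

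Quality of life is a secondary objective under Secondary Objectives, where it is also to be related to dose escalation. The abstract's background paragraph names it within the primary aims. Statistical analysis is descriptive, with full details deferred to the SAP.

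**The concern.** Two adjacent paragraphs combine the same kind of item in two different ways. The subscale rule divides by the number of items that apply, so a child with few applicable items and a child with many are on the same 0–100 scale. The added-item rule drops that division. An item that does not apply then contributes nothing to the sum, which has the same effect as the worst possible answer. An item that starts to apply raises the sum unless it is rated at the very bottom.

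Several added topics, such as verbal communication and use of books, are ones where a caregiver of a very young or severely delayed child could reasonably decide that an item does not apply, and could decide differently at a later visit.

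The design makes this matter more. Each child moves through the dose steps in the same order at monthly intervals (Study design; Sample size determination), and there is no control group. Dose and time on study therefore cannot be separated. If the number of applicable items drifts over the months, the added-item total drifts with it and could be read as a relation between dose and quality of life.

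**Working it through.** The article gives no quality-of-life score or sample-size figure to reproduce, so the check applies the stated rules directly.

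**Inputs from the article.** Item values are 0, 25, 50, 75 or 100. There are 13 added items, aggregated as a plain sum. The subscale rule, for comparison, is the sum divided by the number of items not marked Not Appropriate.

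**Assumptions.** The not-applicable option covers the added items. The numbers of applicable items below are illustrations, because the article gives no rate of not-applicable answers.

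**Formulas.** With *n* applicable items of mean value *m*, the stated total is *n* × *m*. The subscale-type score is (*n* × *m*) / *n* = *m*.

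**1. Same child, same ratings, different number of applicable items (*m* = 50).**

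| Applicable items | Stated sum | Maximum possible sum | Mean |
|---|---|---|---|
| 13 | 13 × 50 = 650 | 1300 | 50 |
| 11 | 11 × 50 = 550 | 1100 | 50 |
| 10 | 10 × 50 = 500 | 1000 | 50 |
| 8 | 8 × 50 = 400 | 800 | 50 |
| 5 | 5 × 50 = 250 | 500 | 50 |

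From 13 to 11 items the sum falls by 100, and 100/650 = 15.4%. From 10 to 13 items it rises by 150, and 150/500 = 30%. The mean stays at 50 throughout.

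**2. The direction of change can reverse.** Baseline: 10 items, mean 50, sum 500. Later visit: 13 items, mean 40, sum 13 × 40 = 520. The ratings have worsened by 10 points per item, yet the total has risen by 20. Any later mean above 500/13 = 38.5 shows as a gain. Because items move in steps of 25, a single child cannot total exactly 520, so that figure is best read as a group average. The nearest attainable value shows the same reversal: 8 items at 50 and 5 at 25 give 400 + 125 = 525, a mean of 525/13 = 40.4.

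**3. A stable item count does not fully cure it.** If the same items apply to a child at every visit, the direction of that child's change is right but its size is not comparable between children. A true gain of 10 points per item is 13 × 10 = 130 with 13 applicable items and 8 × 10 = 80 with 8. A group average of summed changes therefore gives more weight to children to whom more items apply.

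**The case against.** The strongest reply has three parts.

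- **The not-applicable option is inferred.** The article does not say outright that the added items carry it. This stands as a stated assumption, but scoring the items like the other QOLCE items supports it. If the option did not extend to them and all 13 were always answered, the sum would be 13 times the mean and no harm would follow.
- **Summed may be loose wording.** The subscale procedure also begins by adding values before it divides, and scoring the items in the same way could be meant to carry the division over. That is possible. As printed, however, the only aggregation stated for these items is a sum, and the sentence is easily corrected.
- **The reach is small.** The added items have a total of their own and are also examined one by one, the QOLCE-55 total is untouched, and the analysis is descriptive. This stands in full and sets the severity.

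A reader might infer more from the same section, and the article does not support it.

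- **That unanswered items are scored as zero.** The divisor excludes only items marked Not Appropriate, so a very literal reading leaves a blank in the denominator. The article never says blanks count as zero, and handling of missing items is commonly left to the SAP or the scoring manual.
- **That the QOLCE-55 total will often be impossible to compute in children under 4.** A wholly inapplicable subscale would leave the four-subscale mean undefined, and the ages do differ: "The original tool was designed for individuals between 4 and 18 years of age", while the trial enrols children "between the ages of 1–10 years". But the article gives neither the number of children under 4 nor any rate of not-applicable answers, so this is possible, not shown to be likely. A fallback rule is again a matter for the SAP or manual.
- **That the main quality-of-life analysis should be confined to ages 4–10, or change computed only on items answered at both visits.** These are preferences, not corrections of an error.

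**Conclusion.** The rule is wrong as written, with minor severity. A plain sum of items that may be marked not applicable measures the number of applicable items together with quality of life, and it departs from the rule that the same section uses for the subscales. This is a stated rule, not a detail left to a later document.

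The illustrated size is a 15.4% fall when two of 13 items cease to apply with unchanged ratings, and a reversed direction when a fall in the item mean from 50 to 40 coincides with a rise from 10 to 13 applicable items. How often such shifts would occur cannot be judged from the article. The conclusion depends on the not-applicable option covering the added items and on the number of applicable items differing between children or visits.

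The QOLCE-55 subscale rule is coherent when every item is either answered or marked and at least one item per subscale applies, so the point does not extend to quality-of-life scoring as a whole.

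**What to change.** In Quality of life assessment, replace the sum of the 13 added items with the mean of those that are applicable and answered, on the same 0–100 scale as the subscales, and state that the not-applicable option covers these items. The item-by-item presentation can stay.

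As clarifications only, the SAP or scoring instructions could say how a blank item is treated and what happens to the QOLCE-55 total when no item of a subscale applies.

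A mean removes the dependence on the number of items. It does not remove differences in which items apply, so a simple count of applicable added items by visit would help a reader judge any drift.

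The cost is one sentence and a small change in scoring code. No new data are needed, and no child is lost from the analysis provided at least one added item is applicable and answered.
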